#### Cost effectiveness

We use a multi-method approach to collect cost data at 6, 12, 26, 40, and 52 weeks. Since our interventions may influence other common comorbidities of cLBP (e.g., depression [88] and obesity [89]), we measure total medical utilization, not only back-related utilization. Direct medical costs are measured, which consist of the cost of i) implementing the interventions themselves and ii) ongoing medical utilization during and after the intervention. Intervention implementation costs (e.g., non-study-specific staff hours, materials, facility use) are captured from study records and valued at their actual costs. Ongoing medical utilization including visits, hospitalizations, tests, radiology, and medications are taken directly from claims data, the BUMC Clinical Data Warehouse integrated databases, and electronic medical record systems. Direct medical costs are valued at their actual costs to the community health centers and BMC. Any non-insurance reimbursed medical utilization (e.g., acupuncturists, chiropractors, out-of-pocket back-related expenses) are obtained from a cost questionnaire adapted from previous studies [90] and are valued at the reported actual price paid by participants. The validity of the cost questionnaire is supported by a take-home cost diary [91]. The diary acts as a prompt for participants between data collection points to note visits to health practitioners, other health-related expenses, and non-medical direct costs (e.g., travel to yoga classes, childcare). This combination approach takes advantage of the fact that a diary can better capture a broad range of day-to-day costs, but a questionnaire can capture costs in a more consistent format with lower patient burden [92-94]. Direct non-medical costs for this study mainly consist of participants’ actual travel costs to the yoga and PT interventions, any childcare costs during those sessions, and the cost of any sessions attended after the Treatment Phase for patients not randomized to receive structured maintenance yoga or PT. These non-medical costs are valued at the reported actual price paid by participants. Unpaid childcare is valued at an average wage rate [95]. Indirect costs (i.e., lost productivity) for employed participants are calculated as the number of lost productive hours multiplied by a national average cost of employment for each participant’s general job category [96]. Lost productivity costs for those not in the workforce is assumed to be captured by their report of overall quality of life [97]. Lost productivity costs for those looking for work will be considered in sensitivity analyses. QALYs will be calculated based on the Short Form-based 6-Dimensional Measure of Health-Related Quality of Life, which is estimated from the results of the SF-36 using a previously developed algorithm [98,99].

#### Adverse events

The same strategy for collecting adverse event data is implemented across all study arms. Participants are instructed in their study introduction packets to contact the study staff immediately if they believe they have experienced an adverse event that may be a result of their involvement in the study. All participants have 24-hour emergency contact information for the PI and a member of the research staff. Furthermore, all data collections (i.e., 6, 12, 26, 40, and 52 weeks) include questions on whether the participant believes he or she incurred any possible intervention-related adverse events. Unblinded study staff and the PI follow-up on all these reports, as necessary. For this reason the PI may need to be unblinded to the treatment assignment for select participants with adverse events.

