### Data collection

There are six data collection points: baseline, 6, 12, 26, 40, and 52 weeks. Throughout the entire study, participants in all treatment arms are asked to complete their surveys in-person at pre-set times at their nearby community health center or BMC. The paper survey administration is proctored only by study staff blinded to participants’ treatment arm. If participants are unable to complete the surveys in-person, they may complete any post-baseline survey over the phone with a blinded research assistant. All paper surveys are double entered into StudyTRAX™ by blinded research assistants. Any inconsistencies between the two data entries are identified and reconciled.

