#### Analysis of safety

The incidence of adverse events, both overall and for specific events, will be compared between groups using a χ^2^ or Fisher’s exact test, as appropriate. Any participant attending at least one session of yoga or PT will be included in that group for purpose of analysis.

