#### Sample size considerations

For the co-primary endpoints of change in pain or function from baseline to week 12, we assume a one-sided α error = 0.05. If we assume a minimal clinically significant difference of 2.0 points for the 11-point pain intensity scale, then using a 1.0 point non-inferiority margin for pain is reasonable [103]. If we assume 3.0 points on the 23-point RMDQ scale is a minimal clinical significant difference, then choosing a non-inferiority margin of 1.5 for function is reasonable [105]. A common standard deviation of change in all groups is 2.5 points for the 11-point pain intensity scale and 4.35 points for the 23-point RMDQ function scale [24,26].

Using these assumptions, 108 participants in both the yoga and PT group would provide 90% power to detect whether yoga is truly non-inferior to PT in respect to effect on pain. Similarly, 107 participants in both the yoga and PT group would provide 81% power to detect whether yoga is truly non-inferior to PT in respect to effect on function. Using these sample sizes, we would be able to detect at least a 1.4 unit difference in pain or at least a 2.4 difference in function with 90% power for superiority of yoga or PT compared to education. We inflated these sample sizes in order to protect against an estimated dropout rate of 20%. With this adjustment, the target sample size for the yoga and PT groups is 128 participants each. Using a yoga:PT:education 2:2:1 randomization scheme, we need a total of 320 participants (128 yoga, 128 PT, 64 education). Thus, for the co-primary outcomes of pain and function at 12 weeks, we have adequate power to determine non-inferiority between yoga and PT and superiority of yoga and PT to education*.*

We also anticipate adequate power for the longitudinal analyses of the Maintenance Phase data. Incorporation of repeated measures over time increases power by increasing the “effective sample size,” which is a function of the number of participants and the number of total measurements (0, 6, 12, 26, 40, and 52 weeks). Participants who drop-out or who have missing data can still be included in these analyses.

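### Adverse events are collected only if the participant suspects a link to the study, yet their incidence is compared between arms without that restriction

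*Protocol article*

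**What the plan says.** The Adverse events section gives two ways for an event to enter the data.

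- **Spontaneous report.** The introduction packet tells participants to contact staff "if they believe they have experienced an adverse event that may be a result of their involvement in the study".
- **Scheduled report.** The surveys at 6, 12, 26, 40 and 52 weeks "include questions on whether the participant believes he or she incurred any possible intervention-related adverse events".

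Follow-up by staff starts from what these two routes deliver: "Unblinded study staff and the PI follow-up on all these reports, as necessary". The section also states that "The same strategy for collecting adverse event data is implemented across all study arms".

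The Analysis of safety section then says: "The incidence of adverse events, both overall and for specific events, will be compared between groups using a χ^2^ or Fisher’s exact test, as appropriate". It does not restrict this to events that the participant thought were related.

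The blinding described is of staff. Under Data collection, "The paper survey administration is proctored only by study staff blinded to participants’ treatment arm". The article does not state in words that participants know their arm, but the interventions make it evident: group yoga classes, individual PT sessions, or a book with newsletters.

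**The concern.** What is collected and what is tested are different quantities. Collection depends on the participant's causal belief, while the test is described as one of event incidence. The same question in every arm gives equal ascertainment only if participants in every arm are equally ready to connect an event with their assignment. Someone who strained a muscle in the week of a supervised class or session has an obvious candidate cause. Someone who was given a book may have a weaker one.

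Two things are at stake. First, a difference between yoga or PT and education could appear without any difference in harm, or a real difference could be hidden. Second, an event that the participant does not connect with the study, such as a fall at home or a new symptom, has no described route into the safety analysis in any arm. Participants are not well placed to judge causation, so relatedness is better assessed after an event is recorded than used as the condition for recording it.

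**Working it through.** The article gives no figure for the safety comparison, so there is none to reproduce. The check is an illustration of how far unequal attribution could move the test.

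**Inputs from the article.** Target arm sizes are 128 yoga, 128 PT and 64 education (Sample size considerations). The test is chi-square or Fisher's exact (Analysis of safety).

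**Assumed inputs.** The true event risk, the share of events that participants attribute, and a two-sided 0.05 level are not in the article. Full follow-up of the target numbers is also assumed.

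**Formula.** Reported rate = true risk × share attributed. The rejection rate is the sum, over all pairs of event counts (i, j) with p < 0.05, of the binomial probability of i in the first arm times that of j in the second.

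**Equal true risk, active arm (128) versus education (64):**

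| True risk | Attributed, active / education | Reported | Fisher rejects | Chi-square rejects |
|---|---|---|---|---|
| 20% | all events recorded | 20% / 20% | 3.9% | 5.1% |
| 10% | 50% / 25% | 5% / 2.5% | 4.4% | 7.3% |
| 20% | 50% / 35% | 10% / 7% | 6.5% | 9.4% |
| 20% | 50% / 25% | 10% / 5% | 15% | 20% |
| 15% | 50% / 5% | 7.5% / 0.75% | 44% | 54% |
| 20% | 50% / 5% | 10% / 1% | 67% | 75% |

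For example, in the fourth row 0.20 × 0.50 = 0.10 and 0.20 × 0.25 = 0.05.

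**Yoga versus PT (128 each).** With a true risk of 20% and attribution of 50% versus 40%, reported rates are 10% and 8%. Fisher's test rejects in 5.4% of trials.

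**The opposite error.** Suppose true risk is 20% in the active arm and 35% in education. With all events recorded, chi-square finds the difference in 61% of trials. With attribution of 50% and 25%, the reported rates are 0.20 × 0.50 = 10% and 0.35 × 0.25 = 8.75%, and it finds a difference in 6%.

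**Events lost.** At 50% attribution half of events go unrecorded, and at 25% three quarters do.

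**The case against.** There is a fair case on the other side, and parts of it stand.

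- **Other data exist.** Pain and back-related function are collected from everyone at every time point, and global improvement at every follow-up. Visits and hospitalizations come from claims and medical records for the cost analysis, whatever their cause. A reader might infer that worsening pain goes unrecorded in every arm. The article does not support that. What remains is that the safety analysis, as described, does not draw on these data.
- **The threshold is low.** Events need only be possible consequences of the intervention or of being in the study. A reader might conclude that the test measures attribution rather than harm. That goes too far: it measures harm passed through a filter. The low threshold weakens the filter but does not remove it.
- **The book includes exercise.** The education material has an exercise program with chapters on stretching, strengthening and aerobic activity, so participants there can attribute a strain too. A bias against yoga and PT is plausible, but its direction and size are not established.
- **Details are elsewhere.** The article refers to Additional file 5 for adverse event procedures, and that file is not shown. It may contain neutral questions or procedures for serious events, so this point concerns the routes the article itself describes. The article does, however, state the condition for both routes and does not mention a third.
- **The primary comparison is little affected.** Yoga and PT both involve supervised sessions and home exercise, so attribution is likely to be similar in those two arms.

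**Conclusion.** The point holds in a limited form. As the article describes them, both routes for adverse events depend on the participant's belief about a treatment he or she evidently knows, and the planned test does not carry that restriction. Using one strategy in all arms does not cure this, because the filter acts through that belief.

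The mismatch follows from the text, but its effect cannot be sized from the article. Under the assumed reported rates, the Fisher rejection rate with no true difference runs from about 4%, no more than nominal, to 67%. The upper figure needs a tenfold gap in attribution and should not be read as an expected value. A twofold gap gives 4% or 15%, depending on the true risk. The concern applies mainly to yoga or PT versus education. The co-primary efficacy outcomes do not depend on it.

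**What to change.** In the surveys and in the introduction packet, ask participants in all arms about any new or worsened symptom, injury, emergency visit or hospitalisation, regardless of perceived cause. Record relatedness afterwards as a separate field. Compare all events between groups, and report related events separately. Recruitment is still under way (Trial status), so the change can reach later participants; for those already surveyed, account for the questionnaire version in the analysis.

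If Additional file 5 already provides for neutral elicitation, the article's description should say so. If the instrument cannot be changed, label the comparison in Analysis of safety as one of participant-attributed events.

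With all events recorded and an equal true risk of 20%, the test returns to about its nominal level (Fisher 3.9%, chi-square 5.1%).

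The cost is an IRB amendment, a revised packet and survey, more events to log and assess, and two questionnaire versions to handle. The rule in Analysis of safety that counts anyone attending at least one yoga or PT session in that group is a separate matter, and this fix leaves it unchanged.

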#### Policies and procedures

Detailed policies and procedures used by study staff to implement and operationalize recruitment, screening, enrollment, data collection, and adverse event reporting can be found in Additional file 5. These include multiple activities done by research staff to enhance treatment adherence including flexible yoga class schedules, weekly reminder calls, and education check-in calls. The BMC research team meets weekly and reviews the previous week and cumulative data on recruitment, enrollment, retention, and data collection. This approach allows the team to identify potential problems and rapidly initiate possible solutions. This quality improvement process allows for continuous monitoring of participants’ engagement with the study and discussion of any circumstances that deserve added attention.

#### Qualitative interviews

Participants are invited for an interview after the completion of the Treatment Phase based on their individual schedule and willingness to participate. The purpose of collecting qualitative data is to gain subjective insight and detail from participants to complement quantitative data. All participants sign a written consent form prior to the interview. Interviews are approximately 30 to 60 minutes long. Interviewers are not well known to the participants. A semi-structured interview guide (Additional file 6) is used to elicit responses regarding the following: i) motivations and expectations regarding the decision to join the study and participation in the interventions; ii) barriers and facilitators to treatment adherence and home practice; and iii) positive and negative experiences, perceptions, and effects of their participation in the study (e.g., changes in back pain, mood, stress). Interviews are audio-recorded and transcribed verbatim (excluding name and other identifiable information).

### Data analysis

Intention-to-treat (ITT) and per-protocol analyses will be performed for all effectiveness analyses with the ITT analysis considered as the primary method. The ITT analysis will include all patients that participated in the intervention regardless of adherence. Every effort will be made to minimize missing data and participant drop-out or loss to follow-up during the study period. We have accounted for possible drop-out or loss to follow-up by increasing the sample size by 20% in all groups. The “last value carried forward” approach will be used to fill in missing outcome variables; this approach reflects an analysis of the last known value of the outcomes and is thought to be conservative as far as the impact on the treatment effect. If the amount of missing data for outcomes or potential confounders is substantial (i.e., >10%), we will perform an analysis based on multiple imputation for comparison. We will also examine the pattern of missing data in order to discern whether the missing data mechanism could be non-ignorable. A per-protocol analysis will include only those participants who are considered to be adherent to the protocol as defined below.

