**Figure 1 F1:**
[figure not shown]
**Study flow diagram.** The study will recruit 320 participants with chronic low back pain from Boston Medical Center and surrounding affiliated federally qualified community health centers. Participants are randomized after baseline data collection to yoga classes, physical therapy (PT), or education through a self-care book in a 2:2:1 ratio. This year-long study is divided into a 12-week Treatment Phase and subsequent 40-week Maintenance Phase. Yoga and PT participants who have attended at least one intervention session during the Treatment Phase are re-randomized at 12 weeks into a structured maintenance intervention or no structured maintenance intervention. For the participants, we term the no structured maintenance intervention as “Home Practice” only. Education participants continue through the study without any re-randomization.

For the subsequent 40-week Maintenance Phase, there are five separate groups. At the end of the Treatment Phase, yoga participants are re-randomized in a 1:1 ratio to either a structured ongoing maintenance yoga program or no structured maintenance. Similarly, PT participants are re-randomized in a 1:1 ratio to either a structured ongoing maintenance PT program or no structured maintenance. Yoga and PT participants randomized to no structured maintenance are encouraged to continue with home practice. Education participants are not re-randomized and are encouraged to continue to review and follow the recommendations of their educational materials. For the Maintenance Phase, we hypothesize: i) maintenance yoga will be non-inferior to maintenance PT; ii) maintenance yoga will be superior to no yoga maintenance; iii) maintenance PT will be superior to no maintenance PT; and iv) maintenance yoga and maintenance PT will both be superior to education.

In addition, we collect data on medical utilization, out-of-pocket direct and indirect medical costs, implementation costs, and health-related quality of life to compare the cost-effectiveness of yoga, PT, and education from three perspectives: society, third-party payer, and the participant. We hypothesize that yoga will be more cost-effective than PT. Individual interviews using a semi-structured interview guide will be analyzed using qualitative methods. This study was approved by the Boston University Medical Campus (BUMC) Institutional Review Board.

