### Randomization for 12-week Treatment Phase

Randomization occurs after administering the baseline survey. We use the randomization procedure built into our study management system (StudyTRAX™, Macon, GA, USA) to randomize each enrolled participant using a 2:2:1 ratio to yoga, PT, and education, respectively. Permuted variably-sized block randomization with block sizes of 5, 10, and 15 are used.

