### Randomization for 40-week Maintenance Phase

At the completion of the 12-week Treatment Phase, all participants who were initially randomized to the yoga arm and have attended at least one yoga class are re-randomized in a 1:1 ratio to either a structured ongoing maintenance yoga program for 40 weeks or no structured maintenance. Similarly, all participants who were initially randomized to the PT arm and have attended at least one PT session during the 12-week Treatment Phase are re-randomized in a 1:1 ratio to either a structured ongoing maintenance PT program for 40 weeks or no structured maintenance. Yoga and PT participants that did not go to any sessions during the 12-week Treatment Phase do not continue into the Maintenance Phase. Education participants continue into the Maintenance Phase without any re-randomization. They are encouraged to continue to review and follow the recommendations of their educational materials. Re-randomization of yoga and PT participants into their new treatment arms for the Maintenance Phase is done by the study biostatistician ([name]) who has no contact with participants, knowledge of any participant identifying information, or other involvement in enrollment or randomization processes. Each participant eligible for the maintenance phase was assigned a random number using the random uniform function in SAS. For yoga and PT separately, the lower half of random numbers were assigned to maintenance and the larger half of numbers to no maintenance. Participants are notified of their re-randomization group after their 12-week survey by unblinded study staff. A password protected spreadsheet on the study’s network drive is used to document when and how participants are notified of their re-randomization assignment.

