#### Analysis of Maintenance Phase data

For the Maintenance Phase, we hypothesize that i) maintenance yoga will be non-inferior to maintenance PT; ii) maintenance yoga will be superior to no yoga maintenance; iii) maintenance PT will be superior to no maintenance PT; and iv) maintenance yoga and maintenance PT will both be superior to education. To test our hypotheses, we will perform longitudinal analyses on the pain and function outcomes incorporating all measurements across the study period, including baseline and 6, 12, 26, 40, and 52 weeks. We will perform a longitudinal profile analysis to compare the pattern of change in outcomes over the study period with a five-part treatment variable (yoga maintenance, yoga no maintenance, PT maintenance, PT no maintenance, education), time, and their interaction as predictors in the model. The initial model will assume an unstructured covariance to account for the correlation between repeated measures on an individual. A simpler model may be used for the covariance or the model for the means over time if found to be appropriate. No missing data will be replaced in these longitudinal analyses. All available patient data can be included and the analysis will be considered to be unbiased under a “missing at random” mechanism. Additional subgroup longitudinal analyses can be done using only data from those participants who were 12-week completers. We will also compare the change in pain medication usage over time using a generalized estimating equation approach or non-linear mixed effects model to account for the repeated measures of a dichotomous outcome. This approach will parallel the longitudinal analyses for continuous outcomes described above.

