#### Cost effectiveness analyses

From the society perspective, a cost-utility analysis will be performed by comparing the incremental societal costs of one treatment arm over another (direct medical and non-medical costs plus productivity costs) to incremental effectiveness in terms of change in QALYs [52]. This is designated as the “reference case” and can be used by policy makers for the broad allocation of health resources [97,100]. For the third-party payer perspective, incremental costs will only include direct medical costs (direct intervention costs plus ongoing direct medical utilization costs) and will be compared to the incremental QALY impact. This analysis will help determine whether it makes economic sense for yoga to be a reimbursable service for this population. For the participant perspective, cost-effectiveness will be determined by comparing participants’ incremental out-of-pocket costs (travel, childcare, over-the-counter medications, use of non-reimbursed healthcare practitioners, co-payments, cost of yoga or PT sessions attended after the 12-week Treatment Phase by those not randomized to a structured maintenance programs) to their incremental QALY impacts. A bootstrap methodology will be used to estimate confidence intervals [101], and one-way sensitivity analyses will be performed to determine the robustness of our estimates to different assumptions such as to the wage rates used to value productivity [102]. Combined LBP and non-LBP-related healthcare utilization will be used for all of these analyses. Sensitivity analyses using LBP-related utilization only will also be performed. All cost effectiveness analyses will use the ITT principle.

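### The primary set called ITT is limited to people who took part in the intervention, and yoga/PT non-attenders are left out of several later comparisons also meant to be ITT or randomised

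*Protocol article*

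**What the plan says.** The Data analysis section plans ITT and per-protocol analyses, "with the ITT analysis considered as the primary method". The next sentence gives the definition: "The ITT analysis will include all patients that participated in the intervention regardless of adherence". What counts as having participated is not defined for any arm.

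On timing, the section on randomization for the Treatment Phase says "Randomization occurs after administering the baseline survey". Everyone randomised therefore has a baseline value, and participation comes later.

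For the period after week 12, the legend to Figure 1 says "Yoga and PT participants who have attended at least one intervention session during the Treatment Phase are re-randomized at 12 weeks". The section on randomization for the Maintenance Phase adds "Yoga and PT participants that did not go to any sessions during the 12-week Treatment Phase do not continue into the Maintenance Phase", and for the control arm "Education participants continue into the Maintenance Phase without any re-randomization". The longitudinal model is specified "with a five-part treatment variable (yoga maintenance, yoga no maintenance, PT maintenance, PT no maintenance, education"). The cost-effectiveness section closes with "All cost effectiveness analyses will use the ITT principle", and the Specific aims ask for those results at 12 weeks, 6 months and one year.

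**The concern.** An intention-to-treat set keeps everyone in the arm to which chance assigned them. A set that requires participation selects on behaviour after assignment, and the requirement bears unequally on the arms. Yoga means travelling to group classes and PT means attending clinic sessions, whereas education is a book with newsletters, so it is hard to see how someone in that arm would fail to take part. If people who never attend do worse than those who do, removing them flatters the active arms against education. It can also move the yoga–PT contrast, on which the primary non-inferiority claim rests, if non-attendance differs between those two arms.

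After week 12 the same selection is part of the design. Yoga and PT enter the Maintenance Phase as attenders only, and education enters whole. The five-level treatment factor has no level for a yoga or PT participant who was never re-randomised, although the model is to use data from baseline onwards. The cost-utility results at 6 months and one year are said to follow ITT, yet on the natural reading they would lack the non-attenders.

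**Working it through.** **Step 1: what the set contains.** The waiver at the end of the ITT definition covers the degree of adherence. It does not waive the need to have participated. Nowhere does the article say that all randomised participants are analysed as assigned.

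**Step 2: which comparisons are affected.**

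| Comparison | Groups as written | Between randomised groups? |
|---|---|---|
| 12 weeks, yoga vs PT | participants in each arm | not assured |
| 12 weeks, yoga or PT vs education | participants in each arm | not assured |
| Maintenance (i), yoga vs PT | re-randomised attenders in each arm | no |
| Maintenance (ii) and (iii), maintenance vs none within yoga, within PT | attenders re-randomised 1:1 | yes |
| Maintenance (iv), maintenance arms vs education | attenders vs all education | no |
| Cost-utility, 6 months and one year | on the natural reading, yoga/PT without non-attenders vs all education | no, although ITT is stated |

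**Step 3: the plan's own figures.** Inputs from Sample size considerations: one-sided alpha 0.05; margins 1.0 (pain) and 1.5 (function); SD of change 2.5 and 4.35; 108 and 107 per group. With SE = SD × √(2/n) and power = Φ(margin/SE − 1.645):

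- Pain: SE = 2.5 × √(2/108) = 0.340; power = Φ(2.939 − 1.645) = 0.902, against 90% stated.
- Function: SE = 4.35 × √(2/107) = 0.595; power = Φ(2.522 − 1.645) = 0.810, against 81% stated.

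Both reproduce. The problem lies in the definition of the set, not in these figures.

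**Step 4: illustrative size.** The article gives neither a non-attendance rate nor outcomes in non-attenders, so both are assumed. Let a share q of an arm never attend and improve g points less than attenders. Excluding them raises that arm's mean improvement by q × g. The contrast with an education arm that loses nobody moves by q × g. The yoga–PT contrast moves by (q_yoga − q_PT) × g when g is the same in both arms.

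- People removed, q = 5% to 20%: 128 × 0.05 = 6.4 to 128 × 0.20 = 25.6 per active arm.
- Active arm vs education, pain, g = 1 to 2: 0.05 × 1 = 0.05 to 0.20 × 2 = 0.40 points in favour of the active arm.
- Active arm vs education, RMDQ, g = 1.5 to 3: 0.05 × 1.5 ≈ 0.08 to 0.20 × 3 = 0.60 points.
- Yoga vs PT with equal q and equal g: shift 0, one-sided alpha stays at 0.05.
- Yoga 10%, PT 5%, pain, g = 1 to 2: shift 0.05 to 0.10, which is 5–10% of the 1.0 margin. If the true difference in the full randomised groups sits at the margin, the error rate is Φ(shift/0.340 − 1.645), that is Φ(−1.498) = 0.067 to Φ(−1.351) = 0.088.
- If PT had the higher non-attendance, the sign reverses and non-inferiority becomes harder to show.

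**The case against.** The best defence is that the definition is loosely worded. Where the authors mean attendance they say so, as in the re-randomisation rule and the safety set. The ITT sentence contains no such test, and the cost-effectiveness section invokes ITT without listing exclusions. Enrolled may have been intended. That is possible, but the sentence would then still need correcting, because its plain meaning is a condition met after randomisation and no other text overrides it.

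Four stronger readings are tempting, and the article does not support them.

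- A reader might infer that outcomes of non-attenders after week 12 are never collected. The article says they do not continue into the Maintenance Phase, which suggests this. It does not state that their later surveys are omitted, and the Data collection section asks participants in all arms to complete surveys throughout. Detailed procedures are in an additional file that is not shown. Medical utilisation also comes partly from claims and record systems, which do not depend on attendance, although QALYs need the SF-36.
- A reader might infer that every long-term comparison is compromised. Hypotheses (ii) and (iii) are randomised 1:1 among attenders and are valid. Restricting re-randomisation to attenders is not in itself an error.
- A reader might infer that the primary analysis is beyond repair. The 6- and 12-week surveys carry no attendance condition and everyone has a baseline value, so new wording is enough there.
- A reader might infer that the exclusion favours yoga over PT. Nothing in the article indicates which arm would have more non-attenders.

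**Conclusion.** The point holds in this bounded form. The primary set is called ITT but is defined by participation after randomisation, so the 12-week comparisons are not guaranteed to be between the randomised groups. Maintenance comparisons (i) and (iv), and the 6-month and one-year cost-utility analyses, leave out yoga and PT non-attenders. For the cost-utility analyses this conflicts with the stated ITT principle.

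The size cannot be derived from the article. Under the assumed ranges, the bias against education is 0.05–0.40 pain points whenever non-attenders do worse. For yoga versus PT it runs from nothing, with equal rates and gaps, to 0.05–0.10 points and a one-sided alpha of about 0.07–0.09 at 10% versus 5%. These figures illustrate the mechanism and do not predict the result. The correction matters because the definition governs the primary analysis, and because the trial is still recruiting, so later follow-up can still be secured.

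**What to change.** 1. Define ITT as all randomised participants, analysed in the assigned arm whatever their attendance. Call the present set modified ITT, state what participation means in each arm, and keep it as a sensitivity analysis.
2. State that yoga and PT participants with no session, while not re-randomised, are still asked to complete the 26-, 40- and 52-week surveys.
3. Run the initial-arm comparisons at 12 weeks, and the cost-utility comparisons at 12 weeks, 6 months and one year, on all randomised participants.
4. For maintenance comparisons (i) and (iv), either include non-attenders or report the results as non-randomised comparisons among attenders. One way to include them is sequential-randomisation weighting: weight 2 for re-randomised participants, because each had a one-in-two chance of the option received, and weight 1 for non-attenders, counted under both the maintenance and the no-maintenance strategy. Other methods would serve.
5. Leave comparisons (ii) and (iii) restricted to the re-randomised.

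The target of 128/128/64 and the stated power inputs do not change. The 12-week part costs only wording. Following non-attenders after week 12 is a modest change in study conduct: three more surveys each and, under the existing schedule, $50 + $50 + $100 = $200 in gift cards per person, plus staff time.
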